#### Arm A: colectomy by laparoscopy

The colectomy will be performed within 30 days after the randomization, by laparoscopy. The extraction site of the specimen is left to the investigator’s discretion. For left colectomy, colorectal anastomosis must be performed laparoscopically with stapled colorectal anastomosis. The type of anastomosis (stapled or hand-sewn) during right colectomy is left to the surgeon’s discretion.

The decision to convert to conventional surgery will be made by the surgical team. Conversion is defined as an inability to complete all intended laparoscopic steps laparoscopically.

#### Arm B: colectomy by laparotomy

The colectomy will be performed within 30 days after the randomization, by laparotomy. For right colectomy, surgery can be performed by midline or right transverse laparotomy. The type of anastomosis (stapled or hand-sewn) either for right or left colectomy is left to the surgeon’s discretion.

#### Common management in both arms

Immuno-nutrition will be given 7 days prior colectomy following the 2011 recommendation from High Authority for Health (HAS) and French clinical guidelines from the French Society of Anaesthesiology and Reanimation (SFAR, Société Française d’Anesthésie et de Réanimation) [28]. No mechanical bowel preparation will be administered before surgery [29]. Anesthetic evaluation will be performed according to the local practices of each investigator center. Epidural analgesia can be performed but is not required in the present trial. Antibiotic prophylaxis and thrombosis prophylaxis will be done according to local standards without consideration of group designation. Whatever the surgical approach, colectomy will be performed with respect to the oncologic labelled HAS-INCa standards recommendations (determined by the FFCD and updated in 2009 by the Evaluation Commission of the SFCD, *Société Française de Chirurgie Digestive*) [30]. According to these recommendations, the colectomy should be performed with curative intent. Neither prophylactic abdominal drainage nor nasogastric tube should be left in place at the end of the procedure [29, 31]. In the postoperative period, enhanced recovery principles are recommended in both arms but no specific perioperative geriatric management protocol is used in the context of the research. Semi-liquid diet should be given on the first postoperative day. Apart from history of prostatic disease, the bladder catheter should be removed on the first postoperative day. The use of tramadol is not recommended because of the reported increased confusional risk [23].

### Statistical analysis and sample size

This study is multicenter, open-label randomized, 2-arm phase III superiority trial, comparing arm A (colectomy by laparoscopy) versus arm B (colectomy by laparotomy) for patients aged 75 years old or more with uncomplicated colon cancer. The hypotheses for sample size calculation are: (i) H0: there is no difference in overall postoperative morbidity between the two arms; (ii) H1: there is a significant difference, with estimated global morbidities in the laparoscopy and laparotomy groups of 20 and 35%, respectively. With a two-sided α risk of 5% and a power of 80% (β = 0.20) as alternative hypothesis H1, 276 patients will be included in total (138 patients in each arm). No interim analysis will be performed. The endpoints will be analyzed according to the intention-to-treat principle, in such a way that patients who did not receive their allocated surgical procedure were analyzed in the treatment group to which they had been randomized. An additional as-treated analysis will also be done, taking into account intraoperative conversions to the open-surgery group.

Continuous variables will be described via the mean, standard deviation, median, minimum and maximum. Categorical variables will be described using frequencies and percentages. The percentages will be calculated with the missing data item. 95% confidence intervals (95% CI) will be calculated when necessary.

Percentage differences between groups will be compared with the Pearson’s χ^2^ test or Fisher’s exact test, as appropriate. Comparison of continuous data will be done by use of the Student’s t test or the nonparametric Mann-Whitney U test, depending on their distribution. Two-tailed *P*-values <0.05 will be considered statistically significant.

Quality of life will be described preoperatively and 3 months postoperatively in both treatment arms. Rate of patients having a QLQ-C30 or QLQ-CR29 score improved, deteriorated or stabilized at the second quality of life assessment will be reported in each arm with frequency and percent. The weighted means at baseline (preoperative score) and at 3 months will be compared in each arm using the Wilcoxon’s signed-rank test. Based on the study by Osoba and colleagues [32], this analysis will be limited to domains showing a difference of at least 10 points between the two assessments, which can be interpreted as a clinically important change. Mean quality of life changes from baseline will be computed in each arm with 95% CI. The weighted mean differences between both arms will be compared using the nonparametric Mann-Whitney U test.

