### Endpoints

The main endpoint of this phase III study is overall postoperative morbidity, defined as any surgical or medical complications occurring up to 30 days after the surgery. If a patient is discharged from the hospital before this delay, an appointment for an outpatient visit will be given at the 30th postoperative day to finish completing the postoperative morbidity form. Postoperative morbidity will be collected by an independent observer, using a standardized collection form during hospitalization and eventual subsequent out-patient visits. The following specific complications will be documented:
Geriatric complications: postoperative delirium, need for physical restraint, fecal impaction, bedsore, fall, swallowing disorder.Postoperative transfusion.Abdominal infectious complications: anastomotic leakage, intra-abdominal collection at a distance from the anastomosis, wall abscess or cellulitis.Non-infectious abdominal complications: paralytic ileus, hematoma, hemoperitoneum, gastrointestinal bleeding, evisceration.Medical complications: cardiovascular complications including cardiac arrest, acute coronary syndrome without myocardial infarction, myocardial infarction, acute heart failure, heart rhythm disorder, transient ischaemic attack or stroke or other; pulmonary complications including pneumonia, pulmonary embolism, acute respiratory failure, pleural effusion or other; deep vein thrombosis; urinary and nephrological complications including acute urinary retention, lower urinary tract infection, pyelonephritis, acute renal failure or other; catheter complications including lymphangitis, thrombosis, infection or other.

The occurrence of postoperative delirium is a specific complication reported in elderly patients after surgery [23]. This complication will be specifically assessed using the Confusion Assessment Method, an instrument validated for the diagnosis of delirium [24]. Anastomotic leakage will be defined either with the clinical findings of peritonitis or radiologically by computed tomography scan with water-soluble rectal contrast demonstrating endoluminal extravasation or isolated intra-abdominal abscess close to the anastomosis. It will be recorded even if it did not involve surgical management. Post-operative complications will be graded from 0 to V based on the classification system validated by Clavien and Dindo [25].

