### Randomization

After completion of all the screening evaluations and the CGA, a second visit will be performed. All eligible patients will be randomly assigned to one of the treatment arms after ensuring that all the inclusion criteria are satisfied, none of the exclusion criteria apply, and the patient gave his nonopposition to participate in the study. The randomization will be performed electronically on the Cleanweb site (https://cleanweb.aphp.fr/Ctms-02/portal/login). To obtain homogeneous populations among treatment arms, patients will be randomized by minimization (in a 1:1 ratio) owing to the following stratification factors: (i) investigator center; (ii) colon tumour location (right or left side, with respect to the splenic flexure); (iii) stage IV colon cancer (excluding peritoneal disease); (iv) age (75–85 years vs. >85 years).

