### Defining “the elderly” and choice of study population

Aging can be broadly defined as a progressive, generalized impairment of function resulting both in a loss of adaptive response to a stress and in a growing risk of age-associated disease [48]. Although ageing is a complex, multifactorial process, patients are often defined as elderly based on their chronological age. In this trial, the threshold age of 75 years is based on the results of the study by Kurian and colleagues [48]. With the use of the ACS-NSQIP database, the authors identified 129,331 patients who underwent major gastrointestinal resections, with notably 101,258 colectomies (78.3% of included patients). In this large study, it was observed an accelerate increase in the 30-day mortality rate starting at 75 years of age (5.3% per decade). Thus, based on the most recent literature, we consider that for patients requiring colon surgery for cancer the chronologic age of 75 years is a relevant cutoff to define “the Elderly”. As defined by WHO, our study population will include the “middle old” (75–85 years) and the “old old” (85 years or more). Our study will also be stratified on these age’s intervals. However, as age alone cannot properly reflect ageing, all patients who will be included in this trial will have a preoperative CGA with the use of validated scores.

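### The stated χ²/Fisher comparison ignores the four minimisation factors: valid but mildly conservative, forgoing about 0–4 points of power while the planned 80% is still met

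*Protocol article*

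**What the plan says.** In the protocol article, the Randomization section states that "patients will be randomized by minimization (in a 1:1 ratio) owing to the following stratification factors": investigator centre, tumour side relative to the splenic flexure, stage IV disease, and age 75–85 versus over 85. The stated purpose is comparable arms.

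The Endpoints section makes the primary endpoint binary: "overall postoperative morbidity, defined as any surgical or medical complications occurring up to 30 days after the surgery".

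Under Statistical analysis and sample size, the rule for proportions is that "Percentage differences between groups will be compared with the Pearson’s χ^2^ test" or Fisher's exact test. The sample size assumes "estimated global morbidities in the laparoscopy and laparotomy groups of 20 and 35%, respectively", with two-sided α of 5% and 80% power, giving 276 patients (138 per arm). Analysis is by intention to treat. The one additional analysis is as-treated, which moves converted patients to the open group and does not involve the minimisation factors.

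The Discussion section on defining the elderly describes the age strata differently. The older class there is "85 years or more", while the younger one still runs from 75 to 85.

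**The concern.** Minimisation makes the arms alike on the four factors. Any part of the variation in morbidity that these factors explain can then hardly contribute to the difference between arms. An unadjusted 2×2 test still counts that part in its variance. If the factors are prognostic, its standard error is too large, its p-value and confidence interval are conservative, and it has less power than an analysis using the factors. The data needed are already recorded at randomisation.

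The article gives some reason to expect prognostic value:
- **Age.** The Discussion cites mortality ratios of about 3.2 (75–84 years) and 6.2 (85 and over) against patients under 65, so roughly 6.2/3.2 = 1.9 between the two older groups. This is mortality, although the same paragraph also reports higher morbidity in elderly patients.
- **Centre.** The section on common management leaves anaesthetic evaluation and antibiotic and thrombosis prophylaxis to local practice, and makes epidural analgesia optional. Differences between centres in an any-complication endpoint are therefore plausible.

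The age coding matters for the same reason. A covariate should enter the model as it was used in allocation, and the article gives two versions of it.

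**Working it through.** **1. The plan's own figure.** Inputs from the sample-size section: p₁ = 0.35, p₂ = 0.20, so p̄ = 0.275; two-sided α = 0.05; power 80%.

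n per arm = [1.96·√(2·0.275·0.725) + 0.8416·√(0.35·0.65 + 0.20·0.80)]² / 0.15² = (1.2377 + 0.5239)² / 0.0225 = 137.9, so 138 per arm and 276 in total. The stated figure is reproduced. Power at 138 per arm is 80.0% by formula and 80.3% by exact enumeration of the uncorrected χ² test. At about 0.275 × 138 = 38 expected events per arm, Pearson's test is the one that would apply.

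**2. Normal approximation.** Let the factors explain a share R² of outcome variance, with the arms balanced on them, and let f = √(1 − R²). Then:
- SE used by χ² under H0: s₀ = √(0.275·0.725·2/138) = 0.0538; SE under H1 without balancing: s₁ = √(0.3875/138) = 0.0530.
- The unadjusted SE is too large by a factor 1/f.
- Actual α of χ² = 2·[1 − Φ(1.96/f)].
- Power of χ² = Φ[(0.15 − 1.96·s₀)/(s₁·f)]; power adjusted = Φ[(0.15 − 1.96·s₀·f)/(s₁·f)].
- Total N for 80% power with adjustment = 2 × (138·(1 − R²), rounded up).

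R² is an assumption; the documents do not give it.

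| R² | SE too wide by | α of χ² | Power χ² | Power adjusted | N adjusted |
|---|---|---|---|---|---|
| 0 | 0% | 5.0% | 80.0% | 80.0% | 276 |
| 2% | 1% | 4.8% | 80.3% | 80.8% | 272 |
| 5% | 3% | 4.4% | 80.6% | 82.0% | 264 |
| 10% | 5% | 3.9% | 81.3% | 84.0% | 250 |
| 15% | 8% | 3.4% | 82.0% | 86.0% | 236 |

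At R² = 10%, for example, f = 0.949. Power of χ² is Φ(0.0446/0.0503) = 81.3%, and adjusted power is Φ(0.0500/0.0503) = 84.0%.

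**3. Simulation of the allocation.** Minimisation balances margins only approximately, so it was simulated directly: N = 276, 4,000 runs per scenario, biased coin 0.8, marginal rates calibrated to 35% and 20% (27.5% in both arms under the null). The calibration mix was 50% on one tumour side, 12% stage IV and 30% over 85. The adjusted analysis is a risk-difference model on all four factors with robust SE. Number of centres, between-centre SD (logit scale), odds ratios (side/stage/age) and factor mix are all assumptions.

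| Scenario | α: χ² vs adjusted | Power: χ² vs adjusted |
|---|---|---|
| 20 centres, SD 0, ORs 1/1/1 | 4.8% vs 4.7% | 80.3% vs 79.6% |
| 20 centres, SD 0.3, ORs 1.3/1.3/1.5 | 4.8% vs 5.2% | 80.6% vs 80.4% |
| 10 centres, SD 0.5, ORs 1.5/1.5/2.0 | 4.5% vs 5.0% | 80.4% vs 81.7% |
| 20 centres, SD 0.5, ORs 1.5/1.5/2.0 | 4.2% vs 5.1% | 81.7% vs 82.8% |
| 20 centres, SD 0.8, ORs 1.5/2/2.5 | 3.5% vs 5.0% | 80.7% vs 84.2% |

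The Monte Carlo standard error is √(0.05·0.95/4000) = 0.3 points for α and √(0.8·0.2/4000) = 0.6 points for power. A separate simulation with 2,500 runs per scenario gave χ² type I errors of 4.7%, 3.8% and 3.7% for non-prognostic, moderate and strong factors. Power (χ² vs adjusted) was 80.4% vs 79.9%, 80.8% vs 81.8% and 81.9% vs 85.1%.

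In the strong case of the table, a logistic model with side, stage and age but no centre reached 82.3%. Of the 3.5-point gain, slightly more than half therefore came from including centre.

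**4. Age classes.** Randomization: 75–85 versus over 85, so a patient aged 85 is in the younger class. Discussion: 75–85 and 85 or more, with the statement that the trial is stratified on these intervals, so the same patient is in both.

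**The case against.** The strongest reply is that the χ² test is valid here. It does not inflate the type I error, it is the test that 276 patients were sized for, and it delivers its stated 80%. All of that stands. Adjustment is a gain over the plan; leaving it out takes nothing from the plan.

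A reader might infer that the trial is underpowered because of the χ² test, or that a sample size with no margin (137.9 needed, 138 planned) makes the mismatch serious. The documents support neither. At 35% versus 20%, χ² power stays at 80–82% in every scenario above. A clear shortfall needs a smaller true difference: 35% versus 21% gives Φ[(0.14 − 0.1059)/0.0534] = 73.8% by the same formula, whether or not the factors are used.

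A reader might also infer that the four factors were chosen because they drive morbidity. The article says only that they serve to make the arms comparable. It gives evidence for age, mainly on mortality, and none that tumour side, stage IV or centre predicts morbidity.

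Finally, the quoted sentence is a general rule for proportions in a condensed article. Part of the article was not available for review, and a separate SAP may specify an adjusted analysis. That limits the claim to the text at hand. It does not remove the point, because the article names a test rather than staying silent, and that test covers the primary endpoint.

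**Conclusion.** The point holds as a modest inefficiency in the conservative direction. The stated test does not use the factors on which patients were allocated. If those factors predict morbidity, the unadjusted SE is about 1–8% too wide for an assumed R² of 2–15%. In the simulations, type I error is about 3.5–4.5% with moderate to strong factors, and about 0–4 points of power are forgone. With non-prognostic factors the two analyses are equivalent within simulation error. The planned power is met and no false-positive risk arises.

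The direction follows from the design. The size rests on assumed prognostic strength, centre variation and number of centres, which the documents do not quantify. The overlap at age 85 is a plain wording inconsistency that needs no assumption.

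**What to change.** Pre-specify the primary intention-to-treat analysis as a model of 30-day morbidity on arm, tumour side, stage IV and age class exactly as coded at randomisation (75–85 versus over 85). Enter centre as a random effect or pool small centres, since separate terms for many small centres make a logistic model unstable. Report the adjusted (standardised) risk difference and the odds ratio, each with 95% CI. The standardised risk difference keeps the result on the scale of the 35% versus 20% hypothesis. Keep the χ² test as a sensitivity analysis; 276 patients need not change. If a SAP already specifies such a model, bring the article's statement into line with it.

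Align the age classes in the Discussion with those in the Randomization section, so that a patient aged 85 belongs to one class only.

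The cost is protocol or SAP wording; no new data are needed. In an open-label trial the model should be fixed before outcome data are examined by arm.

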## Methods/design

### Protocol overview

The CELL (Colectomy for cancer in the Elderly by Laparoscopy or Laparotomy) trial is a multicenter, open-label randomized, 2-arm phase III superiority trial comparing laparoscopic or open colectomy in elderly patients operated on for colon cancer. For all patients likely to be included in this trial, a comprehensive geriatric assessment (CGA) must be performed within 30 days before the randomization by a geriatrician of the investigator center. This multidimensional evaluation is a major consideration in assessment of operative risk, treatment decision-making, and adapting perioperative care if surgery is undertaken. It aims to determine the medical, psychological and functional capabilities of elderly persons and to distinguish the weakest patients. This diagnostic process will include several reproducible and internationally validated tools, with at least the following scores: the Mini Mental State (MMS) test, the Katz Activities of Daily Living (ADL) scale, the Lawton Instrumental Activites of Daily Living (IADL) scale, the Geriatric Depression Scale (GDS), and the Timed Get-up-and-go (TGUG) test. The general treatment plan is given in Fig. 1.

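### The primary morbidity comparison is unadjusted although geriatric scores are recorded for every patient before randomisation, so a modest, nearly free gain in precision is missed

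*Protocol article*

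**What the plan says.** All points below come from the protocol article.

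- **Primary comparison** (Statistical analysis and sample size): "Percentage differences between groups will be compared with the" Pearson chi-square or Fisher exact test. No covariate is named. The one additional analysis listed there is as-treated.
- **Design assumptions** (same section): "estimated global morbidities in the laparoscopy and laparotomy groups of 20 and 35%, respectively", two-sided 5% alpha, 80% power, 276 patients, 138 per arm.
- **Geriatric assessment** (Protocol overview): every candidate has a comprehensive geriatric assessment (CGA) within 30 days before randomisation, with at least MMS, ADL, IADL, GDS and TGUG. Of its relevance the protocol says: "This multidimensional evaluation is a major consideration in assessment of operative risk".
- **Reason for it** (Defining “the elderly” and choice of study population): "as age alone cannot properly reflect ageing, all patients who will be included in this trial will have a preoperative CGA".
- **Allocation** (Randomization): 1:1 minimisation on centre, tumour side, stage IV disease and age in two bands. No cognitive, functional or frailty score is included.
- **Other uses of the CGA**: eligibility (a positive CGA and MMS of at least 15; exclusion of patients whom the CGA judges unable to tolerate surgery), and a secondary endpoint, change in the scores at 3 months.

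**The concern.** The primary endpoint includes delirium, falls, bedsores and swallowing disorders (Endpoints), for which cognitive and functional state before surgery is plausibly prognostic. The protocol's own reasoning is that age does not capture this state and that the CGA does. Age is nevertheless the only patient-level ageing variable balanced by design, and the primary comparison uses no baseline variable at all.

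Two things are at stake. First, prognostic information already in the database could sharpen the treatment comparison without another patient or visit, in a trial sized at exactly 80% power with no stated allowance for dropout. Second, if the arms differ by chance in frailty, the crude difference carries that imbalance. An adjustment chosen only after the imbalance has been seen would be open to dispute.

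**Working it through.** **1. The plan's own figure.** Inputs from the sample size section: p₁ = 0.35, p₂ = 0.20, difference 0.15, mean 0.275, z-values 1.960 and 0.842. With the pooled-variance formula and no continuity correction:

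n = [1.960·√(2·0.275·0.725) + 0.842·√(0.35·0.65 + 0.20·0.80)]² / 0.15²
= [1.960·0.6315 + 0.842·0.6225]² / 0.0225
= 1.7616² / 0.0225 = 137.9, so 138 per arm and 276 in total.

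Power at 138 per arm is 80.0%. The stated number reproduces for the unadjusted test that the plan names.

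**2. Power with adjustment.** The documents give no figure for the prognostic strength of the scores, so it is assumed and varied. Each scenario used 6,000 simulated trials with 138 per arm and marginal rates held at 35% and 20%. The crude test is the pooled two-proportion test. The adjusted test is the arm effect in a logistic regression.

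| Assumed prognostic strength | Unadjusted | Adjusted | Gain (points) |
|---|---|---|---|
| One score, OR 1.5 per SD | 80.9% | 82.0% | 1.1 |
| One score, OR 2.0 per SD | 80.5% | 83.8% | 3.3 |
| One score, OR 2.5 per SD | 80.5% | 84.8% | 4.3 |
| Three scores, joint AUC 0.64 | 80.4% | 82.2% | 1.8 |
| Three scores, joint AUC 0.69 | 80.1% | 83.6% | 3.5 |
| Three scores, joint AUC 0.74 | 80.5% | 86.0% | 5.5 |

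The Monte Carlo standard error of each power is about √(0.8·0.2/6000) = 0.5 points. Under the null (35% in both arms), rejection was 4.8–5.5% for both methods with one score. With three scores it was 5.2% adjusted and 4.9–5.5% unadjusted.

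A simple approximation agrees. Replacing 138 by 138/(1−R²) gives 80.8%, 82.0%, 84.0% and 86.0% power for R² of 0.02, 0.05, 0.10 and 0.15. For scale, OR 1.5, 2.0 and 2.5 per SD correspond to R² of about 0.035, 0.09 and 0.14 in the laparotomy arm. The total giving about 80% power would be 264 at R² 0.05 and 250 at R² 0.10.

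These runs adjust for geriatric scores only, so any gain from the minimisation factors is not counted.

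**3. Chance imbalance.** For a score that allocation does not balance, the between-arm difference in SD units has standard error √(2/138) = 0.120. The chance that it exceeds 0.2 SD in either direction is 2·[1−Φ(0.2/0.120)] = 9.7%.

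The shift in the crude difference is about 0.2 × (log-odds ratio per SD) × p(1−p):

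- Combined index, log-odds ratio 0.75: 0.2·0.75·0.35·0.65 = 3.4 points at a 35% rate; 0.2·0.75·0.275·0.725 = 3.0 points at the mean rate.
- One of three equal independent scores, log-odds ratio 0.75/√3 = 0.43: 0.2·0.43·0.35·0.65 = 2.0 points.

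The standard error of the crude difference is √[(0.35·0.65 + 0.20·0.80)/138] = 5.3 points, so a 3-point shift is about 0.6 of a standard error.

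**The case against.** The strongest reply is that nothing here is wrong. An unadjusted chi-square test is valid in a randomised trial, holds its type I error, and is the test for which the trial was sized. That stands. A reader might infer that the trial is underpowered or its estimate biased. Neither follows: the stated 80% is delivered, and chance imbalance is random error that the unadjusted interval and P-value already allow for.

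A reader might also infer that a strong prognostic baseline is being thrown away. The documents do not support this either. They link the CGA to operative risk only in words, with no measure of association. Requiring a positive CGA and MMS of at least 15 narrows the spread of the scores, and care adapted to the CGA could weaken the link further. The scores are also used, for eligibility and for a secondary endpoint; only the primary comparison leaves them out. Nor does the remark that age alone does not reflect ageing, made when defining the study population, amount to a statement about balance between arms.

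Finally, adjusted models are often left to the SAP, which is not shown and may contain one. That limits what can be said about absence. But the article does not defer the method: it names an unadjusted test. If an adjusted analysis exists elsewhere, which of the two is primary would still have to be settled.

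**Conclusion.** The point holds as a recommendation on efficiency. The named primary comparison ignores baseline scores that the protocol itself considers relevant to operative risk and does not balance by minimisation. Under the assumed strengths, adjustment would bring power from about 80% to about 82–86%, a gain of roughly 1 to 5 points, with type I error near 5%. Selection at entry may put the true gain at or below the lower end. A 0.2 SD chance imbalance would move the crude difference by about 3 points for a combined index with log-odds ratio 0.75 per SD, and by about 2 points for one of three equal independent scores, against a target difference of 15 points.

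The design figures come from the protocol; the prognostic strengths are assumptions that it cannot confirm. The simulations tested the arm coefficient of the logistic model. Power for the standardised risk difference was not simulated separately.

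**What to change.** In the section Statistical analysis and sample size, and correspondingly in the SAP:

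- Make the primary analysis a prespecified logistic regression of 30-day morbidity on arm. Include tumour side, stage IV disease, age, and a short fixed set of continuous baseline scores, for example MMS, IADL and TGUG. Handle centre in a way suited to small centres, such as a random effect.
- Name the scores before any outcome is seen by arm.
- Report a standardised (marginal) risk difference with 95% CI, so that the result stays on the scale of the design assumption.
- Keep the Pearson chi-square test as a sensitivity analysis.
- State a simple rule for missing baseline scores, such as single imputation of baseline values.

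The cost is wording. The scores are already collected before randomisation, so visits, sample size and conduct do not change. The downsides are the extra rule for what should be few missing baseline scores, and a gain that may turn out small.

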Secondary endpoints are the following: (i) 30-day and 90-day postoperative mortality; (ii) readmission rate. A readmission will be defined in both arms as any rehospitalization within 30 days after discharge from the hospital; (iii) quality of surgical resection. Surgical resection, performed either by laparoscopy or laparotomy, must achieve oncological quality criteria recommended by the French Federation of Digestive Oncology (FFCD, *Fédération Française de Cancérologie Digestive*) and by the French National Authority for Health (HAS, *Haute Autorité de Santé*). Quality and radicality of the surgical excision will be evaluated on histological criteria (number of lymph nodes harvested, R0 resection and mesocolic resection quality in 3 grades); (iv) health-related quality of life. Quality of life will be assessed using the French version the European Organization for Research and Treatment of Cancer Quality of Life Questionnaire Core 30 (EORTC QLQ-C30) version 3.0, with the specific CRC module (QLQ-CR29) [26, 27]. Quality of life will be assessed at the inclusion before surgery and 3 months postoperatively in both treatment arms. The QLQ-C30 consists of 30 items with both multi-items scales and single item measures. The internal validation of QLQ-C30 allowed to identify 15 scales and to generate 15 scores: 5 scores of functional scale, a global health status scale and 9 symptoms scale. All EORTC QLQ-C30 raw scores will be linearly transformed to a value ranging from 0 to 100 according to the EORTC scoring manual. For the 5 functional scales (physical, role, cognitive, emotional and social) and global quality of life scale, a higher score represents a higher level of functioning or quality of life. For the 9 symptom scales and items (fatigue, nausea and vomiting, pain, dyspnea, sleep disturbance, appetite loss, constipation, diarrhea and financial difficulties), a higher score corresponds to a higher degree of symptoms; (v) evolution of geriatric scores (MMS, ADL scale, IADL scale, GDS and TGUG test) at 3 months postoperatively in both arms.

All data of interest will be entered electronically on the Cleanweb site and stored in the patient’s file. An auditing trial will be performed by the Clinical Research Unit of Pitié-Salpêtrière hospital at least twice in each participating center.

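### The between-arm quality-of-life comparison is an unadjusted Mann-Whitney test, although a baseline score is scheduled: it is valid, but generally less precise than baseline-adjusted ANCOVA and yields no mean difference

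*Protocol article*

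**What the plan says.** All references are to the Protocol article.

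- **Schedule** (Endpoints): "Quality of life will be assessed at the inclusion before surgery and 3 months postoperatively in both treatment arms". A baseline score is therefore planned for every patient.
- **Scale** (Endpoints): "All EORTC QLQ-C30 raw scores will be linearly transformed to a value ranging from 0 to 100 according to the EORTC scoring manual".
- **Summary** (Statistical analysis and sample size): "Mean quality of life changes from baseline will be computed in each arm with 95% CI".
- **Between-arm test** (same section): "The weighted mean differences between both arms will be compared using the nonparametric Mann-Whitney U test".
- **Benchmark** (same section): the within-arm signed-rank comparison is restricted, "this analysis will be limited to domains showing a difference of at least 10 points between the two assessments", and a change of that size is treated as clinically important.
- **General rule** (same section): "Comparison of continuous data will be done by use of the Student’s t test or the nonparametric Mann-Whitney U test, depending on their distribution". This is also unadjusted.

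No covariate, ANCOVA or mixed model for quality of life appears in the text available.

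**The concern.** Each patient is scheduled to give a pre-surgery and a 3-month score, so the baseline can be used to sharpen the comparison of arms. The plan uses it only by subtraction, then ranks the differences.

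This has three consequences:

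1. **Precision.** Subtracting the whole baseline is optimal only if the regression slope of the 3-month score on baseline is 1. Otherwise it adds noise that a fitted slope would avoid.
2. **Chance imbalance.** Minimisation balances centre, tumour side, stage IV disease and age group, but not baseline quality of life. If the arms differ at baseline by chance, the change score carries part of that difference into the result.
3. **Mismatch.** The reported summaries are means. Mann-Whitney asks whether values in one arm tend to be larger, and does not estimate a mean difference. The reader would get a between-arm p-value without a matching effect in points, although the plan itself reasons in points.

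At stake is how informative a patient-centred secondary endpoint will be in a trial sized on morbidity alone.

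**Working it through.** **The plan's own figure.** The article gives one sample size, for morbidity (20% v 35%, two-sided 5%, power 80%), and none for quality of life. With a pooled variance and no continuity correction:

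n per arm = [1.960·√(2·0.275·0.725) + 0.842·√(0.20·0.80 + 0.35·0.65)]² / 0.15² = (1.238 + 0.524)² / 0.0225 ≈ 138, or 276 in total.

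The stated figure is reproduced, and nothing below alters it.

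**Relative variance.** Let r be the baseline/3-month correlation and k = SD(3 months)/SD(baseline). In units of the baseline variance:

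- change score: 1 + k² − 2rk
- ANCOVA: k²(1 − r²)
- ratio: (1 + k² − 2rk) / [k²(1 − r²)], which is 2/(1+r) when k = 1

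Numerator minus denominator is (1 − rk)². The ratio is therefore never below 1, and equals 1 only when the slope rk is 1.

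The article gives neither r nor k; both are assumed here.

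| r | k = 0.8 | k = 1 | k = 1.25 |
|---|---|---|---|
| 0.3 | 1.16/0.582 = 1.99 | 2/1.3 = 1.54 | 1.813/1.422 = 1.27 |
| 0.5 | 0.84/0.48 = 1.75 | 2/1.5 = 1.33 | 1.313/1.172 = 1.12 |
| 0.7 | 0.52/0.326 = 1.59 | 2/1.7 = 1.18 | 0.813/0.797 = 1.02 |

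**What that means for the test actually named.** The ratio describes a comparison of mean changes. Under normality Mann-Whitney has efficiency 3/π = 0.955 relative to the t test, a further loss of about 5%. Power was calculated with SD 25 at both times, a true difference of 7 points and 138 complete patients per arm (all assumed). It was also simulated with scores rounded and bounded to 0–100 (2,000 runs per setting).

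| r | SE, change | SE, ANCOVA | Power, Mann-Whitney v ANCOVA (normal) | Power, Mann-Whitney v ANCOVA (bounded, simulated) |
|---|---|---|---|---|
| 0.3 | 3.56 | 2.87 | 48% v 68% | 46% v 65% |
| 0.5 | 3.01 | 2.61 | 62% v 77% | 59% v 73% |
| 0.7 | 2.33 | 2.15 | 84% v 90% | 79% v 86% |

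With no true difference, simulated rejection rates were 4.0% to 5.8% for Mann-Whitney on change and 4.0% to 6.0% for ANCOVA. Both are compatible with the nominal 5%.

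**Chance imbalance.** If the arms differ at baseline by D and there is no treatment effect, the expected difference in change is (rk − 1)·D. With SD 25 and 138 per arm, one standard error of D is 25·√(2/138) = 3.01 points. Such an imbalance shifts the change-score difference by −2.1, −1.5 or −0.9 points at r = 0.3, 0.5 or 0.7 (k = 1). ANCOVA removes this shift when the baseline relation is linear.

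**Mismatch.** In one simulated case with equal mean change but different shapes in the two arms, Mann-Whitney rejected in 6.1% of runs and Welch's t test in 4.2%. The two address different quantities, but in that example the practical divergence was small.

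**The case against.** The strongest reply is that this is a choice of efficiency, not an error. A rank test on change is valid in a randomised trial, the endpoint is secondary and unpowered, and no stated figure or primary conclusion depends on it. Model details are also commonly left to an analysis plan. The first part stands and limits the weight of the point. The last does not remove it: the article leaves no gap here but names the test.

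Several stronger readings are tempting and are not supported:

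- **Bias.** A reader might infer that the planned comparison is biased. It is not: across randomisations the change-score contrast is unbiased. Only the conditional effect of an observed chance imbalance remains.
- **Change always over-corrects when r is below 1.** This holds with equal SDs. What matters is the slope rk, which can equal 1 with r below 1.
- **Patient equivalents.** Multiplying 138 by 1.54, 1.33 and 1.18 suggests that ANCOVA is worth 212, 184 or 162 patients per arm. That needs equal SDs and complete 3-month data, in patients aged 75 or more in a trial that counts 90-day deaths. A scheduled baseline is also not a completed one.
- **No between-arm interval will be given.** The article provides for 95% CIs where needed. A between-arm one for quality of life is not promised, but not excluded.
- **The same fault in the geriatric scores.** The article lists "evolution of geriatric scores (MMS, ADL scale, IADL scale, GDS and TGUG test) at 3 months" without naming a change-score test. Only the general rule for continuous data covers them, and it does not say whether change or the 3-month value is compared.

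Change from baseline is itself a reading, since the article does not define its weighted differences, though the sentence before makes it the natural one. Part of the text directly after the quality-of-life paragraph, and any separate analysis plan, were not available.

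**Conclusion.** The point holds as one of efficiency and interpretability for quality of life. The article fixes a valid but unadjusted rank comparison where a better use of scheduled data is available.

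For mean change scores the variance penalty against ANCOVA is 18% to 54% for r from 0.7 to 0.3 with equal SDs and complete data. If the SDs differ, it can be almost nil (1.02 at r = 0.7, SD ratio 1.25) or considerably larger (1.75 at r = 0.5, SD ratio 0.8). For mean-based comparisons the direction is certain unless the slope is exactly 1; the size is not known from the documents. Against Mann-Whitney specifically, the advantage rests on the normal and bounded-score settings examined, so it is general rather than guaranteed for every skewed scale.

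There is no type I error problem and no effect on the primary endpoint or sample size. The change is worth making.

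**What to change.** - Make the main between-arm comparison of each 3-month QLQ-C30 and QLQ-CR29 score an ANCOVA on arm and baseline score. The minimisation factors may be added.
- Report the adjusted between-arm difference in points with a 95% CI, using robust or bootstrap standard errors for skewed scales.
- Keep Mann-Whitney as a sensitivity analysis, and define what is ranked and what the weights are.
- The same baseline adjustment can be used for MMS, ADL, IADL, GDS and TGUG, where the article fixes no specific change-score test.

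The cost is a few lines of analysis wording, best settled before any comparison of the arms is seen. No visit, questionnaire or patient is added, since both assessments are already scheduled.
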